## Abstract

**Background:**

Functional abdominal pain disorders (FAPDs) affect many children worldwide, predominantly girls, and cause considerable long-term negative consequences for individuals and society. Evidence-based and cost-effective treatments are therefore strongly needed. Physical activity has shown promising effects in the practical management of FAPDs. Dance and yoga are both popular activities that have been shown to provide significant psychological and pain-related benefits with minimal risk. The activities complement each other, in that dance involves dynamic, rhythmic physical activity, while yoga enhances relaxation and focus.

**Objective:**

This study aims to evaluate the effects of a dance and yoga intervention among girls aged 9 to 13 years with FAPDs.

**Methods:**

The study is a prospective randomized controlled trial among girls aged 9 to 13 years with functional abdominal pain, irritable bowel syndrome, or both. The target sample size was 150 girls randomized into 2 arms: an intervention arm that receives dance and yoga sessions twice weekly for 8 months and a control arm that receives standard care. Outcomes will be measured at baseline and after 4, 8, 12, and 24 months, and long-term follow-up will be conducted 5 years from baseline. Questionnaires, interviews, and biomarker measures, such as cortisol in saliva and fecal microbiota, will be used. The primary outcome is the proportion of girls in each group with reduced pain, as measured by the faces pain scale-revised in a pain diary, immediately after the intervention. Secondary outcomes are gastrointestinal symptoms, general health, mental health, stress, and physical activity. The study also includes qualitative evaluations and health economic analyses. This study was approved by the Regional Ethical Review Board in Uppsala (No. 2016/082 1-2).

**Results:**

Data collection began in October 2016. The intervention has been performed in 3 periods from 2016 through 2019. The final 5-year follow-up is anticipated to be completed by fall 2023.

**Conclusions:**

Cost-effective and easily accessible interventions are warranted to reduce the negative consequences arising from FAPDs in young girls. Physical activity is an effective strategy, but intervention studies are needed to better understand what types of activities facilitate regular participation in this target group. The Just in TIME (Try, Identify, Move, and Enjoy) study will provide insights regarding the effectiveness of dance and yoga and is anticipated to contribute to the challenging work of reducing the burden of FAPDs for young girls.

**Trial Registration:**

ClinicalTrials.gov (NCT02920268); https://clinicaltrials.gov/ct2/show/NCT02920268

**International Registered Report Identifier (IRRID):**

DERR1-10.2196/19748

## Introduction

Functional abdominal pain disorders (FAPDs) [1,2] affect 13.5% of school-aged children worldwide [3] and are associated with low quality of life [4]. The prevalence is substantially higher among girls (15.9%) than boys (11.5%) [3]. The negative consequences of FAPDs, such as absence from school [4,5], depression [4,6], and high consumption of medical care [7], pose a considerable burden on children and their families. It is common for pain to be sustained throughout the school years [8-11]. Furthermore, somatic symptoms in childhood predict severe mental illness in adulthood [12]. Specifically, FAPDs in childhood can lead to long-term vulnerability to anxiety later in life, even if abdominal pain resolves [13]. Children need early treatment and preventive strategies to address these symptoms [14] regardless of the presence of co-occurring mental health disorders [12].

For almost 90% of children with chronic abdominal pain, no explanatory organic cause can be identified [15], and psychosocial factors contribute to the development and maintenance of the disease [16]. The predisposing factors and pathophysiological mechanisms of FAPDs include visceral hypersensitivity, altered gastrointestinal motility, and changes in intestinal microbiota, as well as stressful events [3,17], mental health issues, and negative experiences, such as bullying [18]. These children are likely to have poor coping strategies for stressful situations [19]. Thus, interventions and therapeutic modalities that address stress reduction are frequently discussed [3].

There is currently no convincing evidence for treatment or symptom relief with pharmaceuticals [17,20-22] or dietary treatment [23]. Nonpharmacological interventions, such as hypnotherapy and different types of cognitive behavioral therapy (CBT), have shown both short- [17,19,24] and long-term pain relief for children with FAPDs [24]. However, many of these interventions are time-consuming or require specially educated staff [17]. Effective strategies for managing FAPDs in children include reducing both parent and child concerns about the seriousness of the condition and, instead of striving for total pain relief, reducing the disability associated with pain [25] and improving the quality of life for the child [25-27].

Physical activity has been shown to be effective in the practical management of FAPDs [18] by distracting from the pain and improving function. Unfortunately, levels of physical activity among young girls is alarmingly low, which calls for action [28]. Dance is a popular physical activity among young girls [29] that can positively influence physical health outcomes [30], motor skills [31], and psychological well-being [32,33]. Through the expressive, creative, and aesthetic aspects of physical activity, dance holds potential to enhance body awareness and improve poor body image, which in turn strengthens self-esteem [34,35]. In a social context, dance is a cost-effective intervention [36] that can reduce somatic and emotional stress-related problems [37], increase self-rated health [38], and enhance self-esteem [39] and feelings of enjoyment and energy [40-42]. For girls aged 8 to 12 years, multicomponent interventions including dance can lead to improvements in psychological well-being, perceived self-efficacy, and physical self-confidence [43]. Although more research is needed, dance has also been proven to help decrease pain, both for young people [44] and adult women [45-47].

Yoga is a psychophysiological practice with a focus on posture, controlled breathing, and attention [48]. For children, yoga has been shown to improve focus and emotional regulation [49] and to effectively reduce anxiety [50,51] and depression [52]. Yoga has also gained popularity in the treatment of pediatric FAPDs [27,53-55]; studies have shown reductions in abdominal pain frequency [56], pain intensity [56,57], and school absence [57]. For children with irritable bowel syndrome (IBS), yoga has been shown to improve quality of life and physical functioning [58,59] and reduce IBS symptoms [58-60], but more research is needed [20].

A combination of physical and mental training has been shown to be beneficial in reducing stress and increasing quality of life [61]. Coupled together, studies indicate a potentially higher effectiveness than one modality alone [61,62]. Choreographed dance routines to popular music combined with calm breathing meditation has been shown to decrease symptoms of depression and anxiety for homeless women [63].

Dance and yoga have been acknowledged in recent research as pain management for young girls [64] and are both noncompetitive activities that can appeal to girls, which in turn can positively impact participation rates [65]. Dance and yoga can complement each other because dance involves dynamic, rhythmic physical activity, while yoga enhances relaxation and focus [66]. Both dance and yoga focus on body awareness, which has been shown to provide significant psychological and pain-related benefits with minimal risk [67,68], and can also meet young people’s desire to self-manage symptoms with accessible treatment options and to take a more active role in their own care [69]. However, more controlled trials of nonpharmacological interventions are warranted [70], especially for stress-modulated conditions in youth [67]. The novelty of the intervention type and the vulnerability of the target group call for extensive investigation, which we aim to accomplish with a longitudinal randomized design and different methodologies. To our knowledge, dance and yoga for children with FAPDs have not previously been studied.

The overall aim of the study is to evaluate the effects of a dance and yoga intervention among girls aged 9 to 13 years with FAPDs.

## Methods

### Approval and Registration

The study was approved by the Regional Ethical Review Board in Uppsala (No. 2016/082 1-2) and is registered on ClinicalTrials.gov (NCT02920268). Any protocol modifications will be communicated to relevant parties.

### Study Design

This study, called Just in TIME (Try, Identify, Move, and Enjoy), started in 2016 when the first intake was performed and will end in 2023. The study is a prospective randomized controlled trial with 2 parallel groups—an intervention group and a control group—of girls aged 9 to 13 years with functional abdominal pain, IBS, or both. The intervention consists of dance and yoga sessions 2 times a week for 8 months. The control group receives standard care as school health care or primary care. The outcomes are measured at baseline and after 4, 8, 12, and 24 months. A long-term follow-up will be performed 5 years from baseline (Figure 1). At all follow-ups, data are collected for both the intervention and control groups. The trial is being conducted in 2 cities in Sweden.

**Figure 1 figure1:**
[figure not shown]
Flowchart of the protocol.

The study follows the standard methodology of intervention research. This protocol is conducted according to the SPIRIT (Standard Protocol Items: Recommendations for Interventional Trials) guidelines [71], and the description of the intervention follows the TIDieR (Template for Intervention Description and Replication) checklist and guide [72]. The study will be reported according to the CONSORT (Consolidated Standards of Reporting Trials) guidelines [73], COREQ (Consolidated Criteria for Reporting Qualitative Research) [74], and CHEERS (Consolidated Health Economic Evaluation Reporting Standards) [75].

### Study Population

According to international guidelines (Rome IV), FAPDs include functional dyspepsia, IBS, abdominal migraine, and functional abdominal pain not otherwise specified with persisting symptoms 2 months prior to diagnosis [1]. The previous term for these diagnoses according to Rome III was abdominal pain-related functional gastrointestinal disorders (FGIDs) [2].

The Rome III criteria provided the current guidelines during the time of the first study inclusion. The study population includes girls diagnosed with functional abdominal pain or IBS according to the Rome III criteria [2] and with persistent pain after examination at the pediatric center. The girls were aged 9 to 12 years during the first year for intake and 9 to 13 years during the second and third intake years.

#### Inclusion Criteria

Inclusion criteria followed the diagnostic criteria for childhood functional abdominal pain in Rome III [2]: (1) episodic or continuous abdominal pain at least once per week for at least 2 months before diagnosis; (2) insufficient criteria for other FGIDs; and (3) no evidence of an inflammatory, anatomic, metabolic, or neoplastic process that explains the patient’s symptoms.

The following criteria were tested to exclude other illnesses: (1) physical examination including normal growth pattern and (2) laboratory screening, including serological screening with immunoglobulin A antibodies against type 2 (tissue) transglutaminase (TGA-IgA), complete blood cell count, erythrocyte sedimentation rate or C-reactive protein, and urine analysis. A fecal calprotectin test was also included if the girl reported symptoms such as diarrhea.

Diagnostic criteria for IBS in Rome III [2] were used. First, at least once per week for at least 2 months before diagnosis, the patient must have had abdominal discomfort or pain associated with 2 or more of the following at least 25% of the time: (1) improved with defecation, (2) onset associated with a change in the frequency of stool, or (3) onset associated with a change in the form (appearance) of stool. Second, there must be no evidence of an inflammatory, anatomic, metabolic, or neoplastic process that explains the patient’s symptoms.

The following criteria were tested to exclude other illnesses: (1) physical examination including normal growth pattern and (2) laboratory screening including serological screening with TGA-IgA, complete blood cell count, erythrocyte sedimentation rate or C-reactive protein, and urine analysis. A fecal calprotectin test was also included if the girl reported symptoms such as diarrhea.

Persistent pain after examination at the pediatric center was measured with a pain diary at baseline. Girls who reported one or more episodes of pain with a pain score of 4 or higher on the faces pain scale-revised (FPS-r) [76,77] during a full week were eligible for the study.

#### Exclusion Criteria

The exclusion criteria for this trial were (1) contemporaneous celiac or inflammatory bowel disease; (2) difficulty following oral instructions, such as hearing impairment, mental retardation, or language difficulties; (3) simultaneous treatment with CBT; and (4) severe psychological symptoms for which other treatment is needed.

#### Recruitment

Participants were recruited from outpatient clinics, primary health care services, and the public.

We recruited participants from the outpatient clinics of the pediatric departments at the university hospitals in Örebro, Karlskoga, and Lindesberg, Sweden. In the second recruitment year, participants were also recruited from the pediatric outpatient clinic in Västerås, Sweden. All girls aged 9 to 13 years (9 to 12 years during the first year of the study) who had visited one of the outpatient clinics during the previous 2 years because of abdominal pain and had received a diagnosis of IBS, functional abdominal pain, constipation, or abdominal pain received an information letter asking whether they wanted to join the study. All participants were found via local diagnosis registries at the included hospitals. After written consent was received from the legal guardians, the diagnosis according to the inclusion criteria was verified in the medical records or by examination by a pediatrician.

In addition, we recruited girls from primary health care services in the region of Örebro and Västerås. Information letters were delivered to potential participants and their legal guardians in primary care, the counselling unit, and school health services. Interested girls and their legal guardians contacted the research team, who distributed an information letter and the consent form. After written consent was obtained, the research team booked an appointment for an examination at the pediatric clinic (Örebro) or research clinic (Västerås).

Information about the study project was provided by several information channels, such as social media, ordinary media, and websites. Interested girls and their legal guardians contacted the research team, who distributed an information letter and the consent form. After written consent was obtained, the research team booked an appointment for an examination at the pediatric clinic (Örebro) or research clinic (Västerås).

Girls and their legal guardians who consented to the study and were eligible for the study according to the inclusion criteria completed the baseline measurement.

#### Randomization

When the baseline measurement was completed and the eligibility check was accomplished, the sample was randomized into an intervention group and a control group. Randomization was performed by an external statistician using minimization based on pain intensity and age at baseline [78].

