#### Intervention Providers

Each group included 7 to 14 girls and was under the guidance of 2 instructors, one at a time. The instructors had a profession in either health care or pedagogy, had experience working with young people, and were educated in teaching children or adolescents in dance (instructor training) and yoga (ie, registered yoga teacher 200-hour training). Prior to the start of the intervention, all instructors attended a 2-day course administered by the research team. This course consisted of practical instructions from the intervention coordinator about the dance and yoga session according to the standardized program design, including dance choreographies and yoga sequences adjusted to the target group as well as teaching style (nonjudgmental and supporting approach). Lectures about theories and underlying mechanisms and about guidelines and ethical aspects regarding children with FAPDs were also given.

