#### Locations

The intervention took place in studios located in the center of Örebro and Västerås, Sweden, which were easily accessible by bus or walking. The studios had yoga mats and music equipment.

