## Results

Ethical approval was received in March 2016 and the data collection began in October 2016.

In total, 172 participants were recruited in 3 waves and the intervention was performed in 3 periods from 2016 through 2019. In summary, 121 girls were eligible and allocated. A total of 64 participants were allocated to the intervention group, and 57 participants were allocated to the control group. Data collection of the postintervention follow-ups are ongoing and the final 5-year follow-up will be completed by fall 2023. We expect to publish the first results of the study in the beginning of 2021.

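### The plan adjusts only for baseline differences that reach significance and names no centre or intake-wave term, so a sizeable chance imbalance between the two cities could go uncorrected

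*Protocol article*

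**What the plan says.** The Randomization section of the protocol article names two balancing factors: "Randomization was performed by an external statistician using minimization based on pain intensity and age at baseline". Centre and intake wave are not among them.

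The Study Design section states that "The trial is being conducted in 2 cities in Sweden", and the Locations section that "The intervention took place in studios located in the center of Örebro and Västerås, Sweden". Under Intervention Providers, "Each group included 7 to 14 girls and was under the guidance of 2 instructors". The Results section reports that "172 participants were recruited in 3 waves and the intervention was performed in 3 periods from 2016 through 2019". Recruitment changed over time: "In the second recruitment year, participants were also recruited from the pediatric outpatient clinic in Västerås, Sweden". So did the age range, which was "aged 9 to 12 years during the first year for intake and 9 to 13 years during the second and third intake years".

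The Statistical Analysis section fixes three things that matter here:
- The primary outcome is first compared between arms with a Fisher exact test, without covariates.
- Change scores go into a repeated-measures mixed model, adjusted for whatever differs significantly between arms at baseline.
- Univariable and then stepwise logistic regression is used to search for baseline predictors of the primary outcome. The candidate variables are not listed.

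The Covariates section does not name centre or wave either.

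**The concern.** In a two-city trial with three yearly intakes, centre and wave are obvious candidates for differences in case mix and usual care. The stated minimisation does not balance the arms on centre, and the stated analysis brings centre in only if its imbalance happens to reach P<.05.

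That rule asks the wrong question. Under random allocation any baseline difference is due to chance, so the test has nothing to establish. Whether an imbalance matters depends on its size and on how strongly the variable predicts outcome, and the baseline P value measures neither well. With about 60 girls per arm, a difference can be large enough to move the result and still miss significance.

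At stake is a treatment estimate carrying an avoidable chance shift, and a primary test that gives up some power in a trial that allocated 121 girls rather than the planned 150.

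**Working it through.** **Planned effect.** The Sample Size section assumes 30% against 10% responders, two-sided .05 and 80% power. The usual two-proportion formula gives n = [1.96·√(2·0.2·0.8) + 0.842·√(0.3·0.7 + 0.1·0.9)]² / 0.2² = 61.6, so 62 per arm. Then 62 × 1.2 = 74.4, so 75 per arm and 150 in total, as stated. The point below does not depend on this figure; it only sets the yardstick of a 20-point difference.

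**Inputs.** From the Results section: 121 allocated, 64 to intervention and 57 to control. Assumed: 40 girls from Västerås (range 30 to 50), a 20-point response difference between centres, and allocation that ignores centre.

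**Chance imbalance.** The number of Västerås girls in the intervention arm is then hypergeometric (121 girls, 64 drawn). The table shows both ends of the 95% range. The shift is the imbalance × 0.20. P is from the Fisher exact test, which the plan names for dichotomous baseline variables.

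| Västerås girls | Intervention | Control | Imbalance (points) | Shift (points) | P |
|---|---|---|---|---|---|
| 30 | 11/64 = 17.2% | 19/57 = 33.3% | 16.1 | 3.2 | 0.057 |
| 30 | 20/64 = 31.3% | 10/57 = 17.5% | 13.7 | 2.7 | 0.095 |
| 40 | 16/64 = 25.0% | 24/57 = 42.1% | 17.1 | 3.4 | 0.054 |
| 40 | 26/64 = 40.6% | 14/57 = 24.6% | 16.1 | 3.2 | 0.081 |
| 50 | 21/64 = 32.8% | 29/57 = 50.9% | 18.1 | 3.6 | 0.064 |
| 50 | 32/64 = 50.0% | 18/57 = 31.6% | 18.4 | 3.7 | 0.044 |

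Five of these six edge cases would not trigger adjustment; the sixth only just would.

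**Typical size.** With 40 Västerås girls the average absolute imbalance is 6.9 points, a shift of 6.9 × 0.20 = 1.4 points. An imbalance of at least 10 points, hence a shift of at least 2 points, has probability 0.17 to 0.28 if Västerås supplied 20% to 50% of the girls.

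**Against sampling error.** The standard error of the planned difference is √(0.3·0.7/64 + 0.1·0.9/57) = 0.070, or 7.0 points. The 3.4-point edge case is about half of that (3.4/7.0 = 0.49).

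**Test behaviour, by simulation.** With no treatment effect, 64/57 allocated and centre response differences of 0 to 20 points, the unadjusted Fisher test rejects in 3% to 4% of trials. With 20% dropout and an assumed centre split:
- Type I error is about 0.036 for Fisher, and about 0.05 for a Mantel-Haenszel test stratified by centre or by five centre-wave cells.
- At 30% against 10%, power is about 65% for Fisher and about 68% to 72% for Mantel-Haenszel.

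Part of that gain comes from leaving behind the conservatism of the Fisher test (0.036 against a nominal 0.05), not from centre itself.

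**The case against.** The strongest reply is that this is a condensed article, that covariate terms are usually left to a SAP, and that centre could still enter through the logistic search, whose candidates are not listed. That is fair as far as silence goes. It does not cover the adjustment rule, which the article states outright and which a SAP faithful to it would carry forward.

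Several stronger readings are tempting and are not supported:

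- **Systematic bias or false positives.** Allocation is randomised, so imbalance in centre or wave is chance and already lies within the sampling error. If minimisation was in fact run within wave or centre, ignoring this makes the test conservative. Higher error rates appear only if outcomes are assumed to cluster within class groups. That is a different issue, which centre and wave terms would not settle.
- **Waves left unbalanced.** The article describes baseline measurement after the summer holiday, three intakes, and randomisation once baseline was complete. This suggests allocation in batches, so waves are probably roughly balanced, though the text does not say so. Centre is the clearer gap.
- **The raised age limit as a source of imbalance.** Age is itself a minimisation factor, so this is largely covered.
- **A second centre that opened only in year two.** Only the Västerås outpatient clinic is dated to the second recruitment year. Other recruitment there is undated.
- **Different delivery by city.** The Procedures, Modes of Delivery and Adherence sections describe one routine, booster sessions and delivery as planned. No passage shows that standard care differed either.

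It also stands that the 3.4-point figure is an edge case resting on an assumed centre share and an assumed centre effect as large as the planned treatment effect.

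**Conclusion.** The point holds in a limited form. Choosing covariates by baseline significance is a poor rule. In this two-city trial it could leave a centre imbalance of roughly 14 to 18 points unadjusted, as with 25% against 42% at P=0.054. The expected harm is modest: about 1 to 2 points on the treatment difference in typical cases and about 3.4 points at the edge of the 95% range, against 20 planned, together with a few points of lost power. These sizes rest on the assumed Västerås numbers, the assumed 20-point centre difference, and allocation that ignores centre. None of it invalidates the randomisation or the primary test. The change is still worth making because it costs very little and the allocation factors can no longer be altered.

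**What to change.** In the Statistical Analysis section:

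- Remove the rule that adjusts for variables differing significantly at baseline.
- Pre-specify centre (two levels) as a fixed factor in the mixed models and in a Mantel-Haenszel or logistic analysis of the 8-month responder outcome, whatever the baseline P values.
- Add intake wave where cells allow, and write down the rule for merging small centre-wave cells before the outcome data are analysed.
- Present results by centre as descriptive only; they would be too small to support a claim about either city.

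Cost: wording only, since centre and wave are inherent in the study records. The price is a few degrees of freedom and possible sparseness. At the planned rates there would be about 0.30 × 64 + 0.10 × 57 = 25 responders, or about 20 after 20% dropout. Five centre-wave levels in a logistic model would therefore be thin. The two-level centre term should be the minimum, with wave as the addition.
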